### Clinical endpoints

The primary endpoint of the study is to assess the safety of CYT adverse events (AEs) or adverse drug reactions (ADRs) reported by participants, which will be collected.

AEs are defined by the Italian Legislative Decree 211/2003 as “any harmful clinical event that occurs in a patient or in a person involved in a clinical trial that has been given a medicinal/device product and does not necessarily have a causal relationship with this treatment.” Indeed, ADRs are defined as follows: “all untoward and unintended responses to an investigational medicinal product related to any dose administered.” The definition also covers “medication errors and uses outside what is foreseen in the protocol, including misuse and abuse of the product” (Directive 2001/83/EC, Ministerial Decree 30 April 2015-GU No. 143).

For the European Regulation (Directive 2001/83/EC), serious adverse events (SAEs) or serious adverse reactions (SARs) are defined as “any unwanted medical event or device failure that results in the following outcomes: is fatal (causes death), is life-threatening (an event in which the patient was at risk of death at the time of the event), requests hospitalization or extension of hospitalization in progress, determines persistent or significant degree disability or incapacity, corresponds to a congenital anomaly/birth defect, is medically significant, or requires intervention to prevent one of the other outcomes listed above.”

If an AE occurs, the physician, supported by the clinical monitor (CM), will evaluate the event/treatment correlation to determine if an AE could be an ADR. At each visit or follow-up, AEs and ADRs reported by participants will be recorded by the CM in the CRF. In case of an ADR, the physician or the CM will fill out the online reporting form on the AIFA website (https://servizionline.aifa.gov.it/schedasegnalazioni/#/). The textual descriptions will be summarized in the report forms and will be coded according to standard terms in the Medical Dictionary for Regulatory Activities (MedDRA).

The secondary endpoints of the study are to assess the efficacy and compliance of CYT treatment. Self-reported 7-day and 15-day point prevalence abstinence (PPA) will be assessed at each study timepoint. A relapse will occur when patients smoke 7 or more cigarettes for 7 consecutive days or 2 consecutive weeks.

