The decision concerning the patient’s inclusion in the study will ultimately be made by the AMPs and the CM based on the predefined inclusion and exclusion criteria. Any participant who meets the exclusion criteria will not be recruited. Following the collection of baseline data, the AMPs and the CM will then give CYT, prepared by IUHVR’s HPs, to the participants and provide detailed counseling. In case of discharge, CYT will be provided to the patients to continue the therapy at home. CYT will be provided throughout the treatment duration according to the West dosing schedule (25 days, 101 capsules). In the case of patients with chronic kidney failure (stage IV or V), a reduced dosage schedule will be followed, providing 57 capsules.

On the first day of therapy, all participants will be instructed to abstain from smoking and to quit completely (quit day, QD).

Instructions about the West dosage schedule, common CYT ADRs, and emergency contact information will be given to participants by the CM. Finally, a study diary will be provided to support participants to help ensure proper intake of CYT.

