**Figure 1 fig1:**
[figure not shown]
Study protocol timeline. QD, quit day.

After the baseline visit, two visits (visit 1 at day 7 and visit 2 at the end of treatment, day 25) and three follow-ups (visit 3 at 3 months, visit 4 at 6 months, and visit 5 at 12 months) will be conducted (see Table 1). Visits 1, 2, and 3 will be conducted face-to-face. The last two visits (visits 4 and 5) will be conducted via telephone.

**Table 1 tab1:** Protocol timeline procedure of visits and follow-up for patients enrolled in the CITOSP trial.

Procedure	Visit 0	QD*	Visit 1	Visit 2^§^	Visit 3	Visit 4	Visit 5
Informed consent	√						
Inclusion/exclusion criteria	√						
Demographic characteristics	√						
Clinical history	√						
Smoking history and status	√						
Cytisine treatment		√	√	√			
Adverse events			√	√	√	√	√
Adverse drug reactions			√	√	√	√	√
Self-reported abstinence (PPA)			√	√	√	√	√
Biochemically verified abstinence (exhaled CO)			√	√^#^	√^#^		

QD, quit day.

PPA, point prevalence abstinence.

CO, carbon monoxide.

^#^Only if the visit is in person.

*First day of treatment. ^§^Stop treatment.

Each control visit resulted in the collection of the following records:

Visit 0 (baseline visit): informed consent dated and signed, participant identification code, and socio-demographic characteristics of the participant (age, sex, education, and occupation). Smoking history: age at which cigarettes were first smoked and efforts to quit smoking (number of times, date of last attempt, and use of some drugs to quit smoking). Smoking Status: average amount of cigarettes smoked in the last month, average cigarettes for the year, the score obtained in the FTND test, and use of other forms of nicotine delivery (for example, e-cigarettes). Clinical history: pathologies and ongoing pharmacological treatments. Integrated therapeutic: This statement outlines the non-pharmacological approaches used in the study to help patients, including counseling, cognitive-behavioral education, lifestyle changes, and the possible use of smoking cessation tools.

QD (first day of abstinence): start of integrated therapeutic plan with CYT.

Visit 1 (7^th^ from QD): continuation of the integrated therapeutic plan with CYT, evaluation of AEs, evaluation of ADRs, evaluation of PPA, number of cigarettes smoked (in case of quit failure), and exhaled CO.

Visit 2 (25^th^ day from QD): end of treatment with CYT, evaluation of AEs, evaluation of ADRs, evaluation of PPA, and exhaled CO.

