### Cytisine dosing schedule

The West dosing schedule consisted of six 1.5 mg capsules per day (one capsule every 2 h) for 3 days (days 1 to 3), five capsules per day for 9 days (days 4 to 12), four capsules per day for 4 days (days 13 to 16), three capsules per day for 4 days (days 17 to 20), and two capsules per day for the final 5 days (days 21 to 25) (see Table 2). The target quit date was scheduled for the first day of treatment (day 1) (7).

**Table 2 tab2:** West dosing schedule (7).

Day of treatment	N° of capsules/die	Frequency of administration
Days 1–3	6	1 capsule every 2 h
Days 4–12	5	1 capsule every 2.5 h
Days 13–16	4	1 capsule every 3 h
Days 17–20	3	1 capsule every 4 h
Days 21–25	2	1 capsule every 6 h

In the case of patients with stage IV or V chronic kidney failure, the CYT dosing schedule consisted of three 1.5-mg capsules per day for 12 days (days 1 to 12), two capsules per day for 8 days (days 13 to 20), and finally one capsule per day for the last 5 days (days 21 to 25) (see Table 3).

**Table 3 tab3:** Cytisine dosing schedule adapted to patients in stage IV or V chronic kidney failure.

Day of treatment	N° of capsules/die	Frequency of administration
Days 1–12	3	1 capsule every 4 h
Days 13–20	2	1 capsule every 6 h
Days 21–25	1	1 capsule every 12 h

Concomitant medication use during CYT treatment will be allowed, evaluated, and documented at each visit, and any possible interactions with CYT will be verified.

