### Sample size and statistical analysis

Assuming an overall incidence of all AEs and ADRs equal to 20% as reported by Hajek et al. (28), 264 subjects will be needed to produce a bilateral confidence interval of 95% with an amplitude of 10%. This number will be increased to 300 subjects to compensate for a potential loss of 14% of subjects during the 12-month follow-up. To recruit 300 subjects, it will take 36 months. The total duration of the study will be 4 years.

All variables recorded in the study will be presented using the plus descriptive statistic appropriate to their nature. Continuous variables will be presented with mean and standard deviation with median and interquartile distance based on their distribution; ordinal and categorical variables will be presented with frequency and percentage.

To assess the safety of treatment with CYT, the incidence of AEs and ADRs will be evaluated, with respective 95% confidence intervals (CIs) up to the end of treatment (day 25) and up to 12 months from the start of the treatment (quit day). The percentage of subjects will be calculated to assess the compliance of patients with CYT treatment who respected their dosage schedule with the respective 95% CI.

To evaluate the efficacy of CYT treatment, the percentage of subjects who reported abstinence in the previous 7 days and 15 days (7-day PPA and 15-day PPA) before each study timepoint will be calculated. For in-person visits and follow-ups, the PPA will be biochemically verified through exhaled CO measurement.

The efficacy will also be studied at a multivariate level to assess whether the positive/negative outcome of the treatment is associated with certain demographic and/or clinical factors. For this type of analysis, they will construct logistic regression models by setting the (yes/no) relapse evaluated as dependent variables according to the reported and objective efficacy criteria at the end of treatment (25^th^ day from the start of treatment) and 12 months from the start of treatment. The independent variables will be chosen based on the assumptions of experimenters on possible predictors of efficacy, including the result of the FTND, the ward, the primary cause of admission, sex, age, education, occupation, age in which the person started smoking, and number of previous smoking cessation attempts.

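### At visit 1 (day 7), 8 to 9 of the 15 look-back days for 15-day abstinence fall before quit day, so that one percentage is not a treatment outcome

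*Protocol article*

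**What the plan says.** The section Clinical endpoints of the protocol article sets the rule for the secondary efficacy endpoint: "Self-reported 7-day and 15-day point prevalence abstinence (PPA) will be assessed at each study timepoint". The section Sample size and statistical analysis repeats it as an analysis, in the form of a percentage that serves as the measure of efficacy: "reported abstinence in the previous 7 days and 15 days (7-day PPA and 15-day PPA) before each study timepoint will be calculated".

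The section Visits and follow-ups schedules "two visits (visit 1 at day 7 and visit 2 at the end of treatment, day 25", followed by visits at 3, 6 and 12 months. Point prevalence abstinence (PPA) is marked for visit 1 in Table 1, and the visit list gives the content of visit 1 as "continuation of the integrated therapeutic plan with CYT, evaluation of AEs, evaluation of ADRs, evaluation of PPA", together with cigarettes smoked and exhaled CO.

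Quit day is tied to the start of treatment. Under Participant recruitment: "On the first day of therapy, all participants will be instructed to abstain from smoking". Under Cytisine dosing schedule: "The target quit date was scheduled for the first day of treatment (day 1". Participant recruitment also says that the patients referred are current smokers. Nothing in the article exempts visit 1 from the 15-day measure.

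**The concern.** A look-back of 15 days cannot fit into the week between quit day and visit 1. The remainder of the window covers days on which the patient had not been asked to stop and had received no cytisine. Success on 15-day PPA at visit 1 therefore depends partly on behaviour before treatment, although the statistical section presents it as evidence of efficacy.

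The study has a single arm, so readers will judge efficacy largely from the abstinence percentages across visits. At stake is whether the first of the 15-day percentages can be read as an effect of treatment, or set beside the later ones.

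**Working it through.** The plan gives no figure of its own here. The check is a count of days.

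**Inputs**
- Look-back length L: 7 or 15 days (Clinical endpoints; Sample size and statistical analysis).
- Visit 1 on day 7 and visit 2 on day 25 (Visits and follow-ups).
- Quit day is day 1 of treatment (Cytisine dosing schedule). Day 0 is tried as an alternative, because the visit list counts days from quit day.
- The article does not say whether the visit day belongs to the window, so both choices are tried. The statistical section speaks of days before the timepoint, which favours leaving it out.

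**Formula**

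Days before quit day = max(0, L − k), where k is the number of days from quit day to the end of the window, counting quit day.

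**Visit 1 (day 7)**

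| Quit day | Visit day counted | k | 15-day window: 15 − k | 7-day window: max(0, 7 − k) |
|---|---|---|---|---|
| day 1 | yes | 7 | 8 of 15 (53%) | 0 of 7 |
| day 1 | no | 6 | 9 of 15 (60%) | 1 of 7 |
| day 0 | no | 7 | 8 of 15 (53%) | 0 of 7 |
| day 0 | yes | 8 | 7 of 15 (47%) | 0 of 7 |

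The last row departs from the article's day-1 numbering and from its wording of days before the timepoint. Under day-1 numbering the answer is 8 or 9 of 15.

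**Visit 2 (day 25)**

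Here k is 24 to 26, so 15 − k is negative and 0 of 15 days precede quit day under every convention. The same is true at 3, 6 and 12 months.

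**What this means for an individual patient**
- Smoked up to quit day, then complete abstinence: not abstinent on 15-day PPA at visit 1, abstinent on the same measure at visit 2. The patient's smoking did not change between the two visits; only the window did.
- Scored abstinent on 15-day PPA at visit 1: must have been abstinent for the 8 or 9 days (7 on the most lenient count) before quit day as well, for example because of the admission.

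Exhaled CO at visit 1 does not repair this. The section Carbon monoxide measurement treats a low reading as confirming no smoking in the days before the visit, so it cannot supply abstinence before quit day for someone who was then smoking.

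**The case against.** The strongest reply is that almost nothing depends on this number. The primary objective is safety, and the sample size rests on the incidence of adverse events. PPA is a secondary percentage, with no comparator and no planned test between visits. The logistic regressions use relapse at day 25 and at 12 months, so day 7 does not enter them. 7-day PPA is planned at the same visits and provides a day-7 to day-25 series beside the 15-day one. All of this stands, and it limits the point to one cell of one descriptive table.

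Two stronger readings are tempting and go too far. A reader might infer that 15-day PPA at visit 1 will be close to zero by construction. The article does not support that. The patients are inpatients, the Discussion notes that cessation is often mandatory for hospitalised smokers, and the time from admission to quit day is not given. The share already abstinent for a week or more before quit day cannot be calculated. A reader might also infer that the report will show a false rise in abstinence from day 7 to day 25. The two figures are not comparable, but no contrast or trend between those visits is planned, and the size of any apparent rise is unknown for the same reason.

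It might also be said that such detail belongs in a statistical analysis plan. That does not answer the point: the article states the rule positively, in two sections, and the rule fails at a visit it names.

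**Conclusion.** The point holds, with limited reach. As written, the plan reports as efficacy a 15-day rate at visit 1 for which 8 to 9 of the 15 days precede quit day under the article's own numbering, and 7 of 15 on the most lenient count. The statement that more than half of the window is before treatment therefore holds under three of the four conventions, including both that use day 1. Under all four, complete abstinence from quit day on is not enough to be scored abstinent.

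The conclusion assumes that the window is applied literally at visit 1, as both sections say. It needs no assumption about how many patients stopped smoking before quit day, and it supports no prediction of the rate. The primary safety endpoint, 15-day PPA at visits 2 to 5, and the regressions are unaffected. The point is worth correcting because the figure is labelled efficacy and the correction is simple, not because it threatens the study's conclusions.

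**What to change.** - In Clinical endpoints and in Sample size and statistical analysis, plan 7-day PPA at visits 1 to 5 and 15-day PPA at visits 2 to 5 only.
- Describe 7-day PPA at visit 1 as abstinence since quit day, and state whether the visit day counts. With quit day as day 1 and the visit day left out, the 7-day window also starts one day before quit day; counting the visit day removes this.
- Table 1 names no window and its PPA row remains correct at visit 1. At most, add a footnote that visit 1 is 7-day PPA only.

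The cost is a change of wording and the loss of one percentage that cannot be interpreted. No visit, sample size or other analysis changes.

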Biochemically verified abstinence will be evaluated using exhaled carbon monoxide (CO) measurement during in-person visits. A relapse is considered when CO value ≥9 ppm (non-smoker value <4.5 ppm) (30, 31).

To assess CYT treatment compliance, patients will be provided a study diary in which capsule intake or self-reported treatment adherence can be reported.

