### Carbon monoxide measurement

The exhaled CO concentration will be measured using the piCOTM Smokerlyzer® (Bedfont Instruments; Kent, United Kingdom), a non-invasive method for assessing the smoker status. It has been reported that the concentration of CO is closely related to the concentration of carboxyhemoglobin in smokers’ and non-smokers’ blood. The piCOTM Smokerlyzer® measures CO levels in the air in parts per million (ppm) based on the conversion of CO to carbon dioxide (CO_2_) on a catalytically active electrode (33).

Scores from 0 ppm to 6 ppm confirm that patients have not smoked cigarettes in previous days before the visit, scores 7 ppm and 8 ppm indicate that patients are light smokers; scores greater or equal to 9 ppm confirm that patients are heavy smokers.

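### The protocol's two CO classifications conflict: 5–6 ppm is read two ways, and 7–8 ppm is light smoking in one section but no relapse under the CO rule in another

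*Protocol article*

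**What the plan says.** Clinical endpoints introduces CO as the means of checking abstinence: "Biochemically verified abstinence will be evaluated using exhaled carbon monoxide (CO) measurement during in-person visits". The next sentence gives that section's only CO decision rule: "A relapse is considered when CO value ≥9 ppm (non-smoker value <4.5 ppm".

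Carbon monoxide measurement describes the same reading in three bands:
- The lowest band, 0–6 ppm, is taken as showing no smoking in the days leading up to the visit.
- The middle band is worded as follows: "scores 7 ppm and 8 ppm indicate that patients are light smokers".
- The top band, 9 ppm or more, is taken as confirmation of heavy smoking.

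Sample size and statistical analysis uses CO in two ways. It verifies abstinence: "For in-person visits and follow-ups, the PPA will be biochemically verified through exhaled CO measurement". It also enters the regression, which is built by "setting the (yes/no) relapse evaluated as dependent variables according to the reported and objective efficacy criteria at the end of treatment" and again at 12 months.

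Relapse by self-report has its own definition in Clinical endpoints: "A relapse will occur when patients smoke 7 or more cigarettes for 7 consecutive days or 2 consecutive weeks".

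**The concern.** Biochemical verification is there to catch people who report abstinence but smoke. That requires one stated reading above which a report of abstinence is not accepted. The article offers several candidates that disagree, and its only explicit decision threshold, 9 ppm, is the lower edge of its own heavy-smoking band.

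Two things are at stake. First, analysts could verify PPA at below 4.5 ppm, at 6 ppm or less, or at below 9 ppm. Each could cite the article, and each could report a different rate from the same readings. If the choice is left until the data are seen, the result can influence it. Second, the yes/no objective outcome at day 25 would place people whom the article calls light smokers on the success side.

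**Working it through.** There is no sample size or power figure to reproduce here. The check classifies each whole-number CO reading under every rule in the article and follows the result into the analyses.

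**Inputs**
- Clinical endpoints: relapse at 9 ppm or more; non-smoker value below 4.5 ppm.
- Carbon monoxide measurement: 0–6 ppm not smoked; 7–8 ppm light smoker; 9 ppm or more heavy smoker.

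**Classification**

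| CO (ppm) | Bands in Carbon monoxide measurement | Non-smoker value in Clinical endpoints | CO relapse rule |
|---|---|---|---|
| 0–4 | not smoked | met | not relapsed |
| 5–6 | not smoked | not met | not relapsed |
| 7–8 | light smoker | not met | not relapsed |
| 9 or more | heavy smoker | not met | relapsed |

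The sections agree at 0–4 ppm and at 9 ppm or more. At 5–6 ppm one section confirms no smoking and the other puts the reading above the non-smoker value. At 7–8 ppm both sections put the person outside non-smoking, yet the CO rule does not count a relapse.

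**What moves under each choice of cut-off**
- From below 9 ppm to 6 ppm or less: readings of 7 and 8 ppm change from success to failure.
- From below 9 ppm to below 4.5 ppm: readings of 5, 6, 7 and 8 ppm change.

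**Where it reaches**
- CO is read at visit 1 (day 7), and at visits 2 and 3 (day 25 and 3 months) if they are in person (Table 1). Verification of PPA is affected at these visits only.
- The logistic models are set at day 25 and 12 months. Visit 5 at 12 months is by telephone without CO, so only the day-25 objective model is affected.
- The primary endpoint is safety and uses no CO reading. The sample size is set by the adverse-event incidence.

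**Size**
Let A be the abstinence rate verified at below 9 ppm, and s the share of those verified who read 7–8 ppm. The rate at 6 ppm or less is then A × (1 − s). The article gives neither A nor s. As a pure illustration, assume A = 30% and let s run from 5% to 15%:
- s = 5%: 30% × 0.95 = 28.5%
- s = 15%: 30% × 0.85 = 25.5%

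These inputs are assumptions, and the sum applies only if PPA is in fact verified at below 9 ppm, which the article does not say.

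**The case against.** The strongest reply is that relapse and abstinence are different concepts. The self-report rule already sets relapse above any smoking, since it requires a minimum amount sustained over one or two weeks. A higher CO threshold for relapse fits that, and a light smoker who has not relapsed is then no contradiction. The 4.5 ppm figure sits in parentheses beside cited sources and assigns nobody an outcome. A person at 7–8 ppm can still be counted as relapsed by self-report. An analysis plan that is not shown could fix the cut-off for PPA.

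Much of this stands. A reader might infer that verified abstinence is known to be inflated. The article does not support that: nowhere does it say that PPA is verified at below 9 ppm, and the 0–6 ppm band may be the one intended. Nor can it be said that light smokers escape relapse altogether, because that is true only of the CO criterion.

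The reply does not remove the conflict. The 9 ppm rule follows directly on the sentence about verified abstinence, and nothing says it is a deliberately higher threshold. If two concepts are meant, a cut-off for verified abstinence is still needed, and the two sections disagree on the non-smoking value. Self-report is no safeguard for people whose self-report is wrong. This is also not detail left to another document: the article states thresholds that conflict, and an analysis plan would have to overrule one of them.

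**Conclusion.** The concern holds in a limited form. The two sections classify 5–6 ppm differently. On the CO criterion alone, 7–8 ppm is not a relapse although the article calls these patients smokers. The consequence is an undefined verification rule for PPA at day 7, day 25 and 3 months, and a day-25 objective outcome that, as written, counts protocol-defined light smokers as non-relapses.

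Only the direction at 7–8 ppm is certain: relative to the 0–6 ppm band, a 9 ppm rule can raise objective success but never lower it. The amount cannot be computed, and the illustrative figures should not be read as an estimate of bias.

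This should be fixed, but it is not critical. Efficacy is a secondary objective in a single-group observational study. The safety endpoint, the sample size and the 6- and 12-month telephone assessments are untouched.

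**What to change.** - State one CO cut-off for verified abstinence in Clinical endpoints, Carbon monoxide measurement, and Sample size and statistical analysis. Taken from the article's own band: self-reported abstinence and CO of 6 ppm or less is verified abstinent; 7 ppm or more is not verified abstinent.
- Use that yes/no variable as the objective efficacy outcome in the day-25 logistic model, and name it as verified abstinence. It then does not clash with the self-report relapse rule, which allows some smoking.
- If 9 ppm is kept, label it either as a deliberately higher threshold for relapse or as a sensitivity cut-off, and say that it does not define verified abstinence.
- Remove the 4.5 ppm value or align it with the 0–6 ppm band.

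The cost is a few words in three sections. No new data are needed, since the CO readings are already planned. Verified abstinence may be slightly lower than under a 9 ppm rule.
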